11. Clinical laboratory	• Blood test a. Biochemistry b. Hormone c. Hematology • Urine test • Omics test e. Metabolomics/lipidomics f. Proteomics	The blood test will be performed using a QDR 2000 densitometer machine (Hologic Inc., America). a. The biochemistry will be used to check the levels of Albumin, AST, TP, Total bilirubin, Ca, Cl, Pi, Na, ALP, Amylase, CK, ALT, LDH, γ-GTP, BUN, Creatinine, Uric acid, Total cholesterol, HDL cholesterol, Triglyceride, LDL cholesterol, and Glucose through blood analysis. b. The hormones to be checked are 25-OH Vitamin D, Osteocalcin, Cortisol, Free T4, TSH, DHEA-S, Vitamin B12, Insulin, GDF8, GDF15, Testosterone, PSA, FSH, LH, and Estradiol. c. The hematology test will check the following: white blood cells, red blood cells, hemoglobin, hematocrit, platelets, mean corpuscular volume, mean corpuscular hemoglobin, mean corpuscular hemoglobin concentration, neutrophils, lymphocytes, monocytes, eosinophils, basophils, and glycated hemoglobin. d. We will be checking the following items in a urine test: Urine WBC, Specific gravity, pH, Protein, Glucose, Occult Blood, Ketones, Urobilinogen, Bilirubin, Nitrite, WBC, RBC, Epithelial cell, Bacteria, Casts, Crystal, Other e. GC/LC-MS based untargeted metabolomics analysis will be conducted to profile the comprehensive metabolic data from blood of participants f. Beads-based multiplex immunoassay will be executed to acquire the proteomics data of blood	1,3

Biological factors: sex, age, weight, height, body mass index, blood pressure, pulse rate, body temperature, overall wellness status, smoking and alcohol consumption history, physical activity, nutritional status, dietary survey, appetite, intake of health supplements, degree of constipation, comorbidities, activities of daily living, physical resilience, oral health status, gynecological history, medical history, surgical history, medication history and family medical history, physical performance test, range of motion assessment for the knee and lumbar joints, core muscle strength measurement, grip strength measurement, hearing, vision, pulmonary function, pulsometry, brain wave examination, bone density, body composition, clinical laboratory examination (biochemical markers, hormones, hematological markers, urine test), and omics profiles (metabolomics/lipidomics, proteomics).

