### Statistical analysis

We will conduct various analyses within the cohort. The results of the participants’ demographic data, the questionnaire-based prevalence of age-related symptoms and KM-based phenotype, physical function, and other outcome variables will be summarized using descriptive summary measures. For continuous outcomes, both univariate and multivariate linear regression analyses will be employed, while logistic regression will be used for dichotomous outcomes. Specifically, group differences (between KM-based phenotypes or between rural and urban areas) will be analyzed using Student’s t test and analysis of variance. The relationships between KM-based phenotypes and physical and psychological health, as well as demographic variables, will be analyzed using multiple regression.

Additionally, missing data patterns will be examined, and appropriate methods for handling missing data, such as Last Observation Carried Forward (LOCF) or Multiple Imputation, will be applied. Mixture models will be utilized to identify subgroups of subjects based on their biological and psychological characteristics. To estimate the cumulative risk of outcomes, Kaplan‒Meier analysis will be employed. Adjustments for covariates will be made before the follow-up period, during which Cox proportional hazard models will be used to estimate the risk of experiencing any of the outcomes. In addition, prediction modeling will be attempted by incorporating new covariates under investigation. P values less than 0.05 will be considered to indicate statistical significance. All statistical analyses will be conducted using SAS® version 9.4.

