## Results

In the baseline phase of this study, we will focus on identifying markers for KM-based phenotypes and examining how these phenotypes relate to aging and associated diseases. In the next phase, we will implement interventions tailored to KM-based phenotypes to verify the effects of KM on healthy aging. Ultimately, we intend to develop a KM-based integrated health management model, with further substudies aiming to explore factors related to healthy aging.

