## Discussion

South Korea is currently navigating the challenges of transitioning into a super-aged society, emphasizing the critical importance of proactive health management for healthy aging before individuals reach the age of 65 years [1–5]. This paper outlines a multifaceted research protocol aimed at revealing the complexities associated with aging in both urban and rural settings, considering the distinctive characteristics that are prevalent in various regions of Korea. Data collection for this study began in August 2023 and is being carried out in two phases. Phase I comprises a cross-sectional cohort study (baseline) detailed in this paper. Participants who are included in the cohort will be given the option of allowing their data to be used for analyses and identifying them for future research interventions or for comparison purposes for intervention trials. Details of the phase II interventions will be published in full manuscripts separately.

In particular, a key aspect of our study involves analyzing KM-based phenotypes to examine aging patterns and certain diseases associated with each phenotype and evaluating the KM-based integrated health management model. To achieve this goal, in phase I, our initial focus is on identifying diagnostic markers that enable the application of KM by conducting multi-omics analyses, including hormone, immune, metabolite markers. We will subsequently explore age-related symptoms or vulnerable diseases associated with KM phenotypes through cohort studies. In phase II, we plan to conduct multiple randomized controlled trials that apply interventions such as community programs specifically tailored to well-defined KM-based phenotypes identified in phase I to verify the effects of KM on healthy aging. Based on these results, we intend to develop an integrated health management model for healthy aging, and establish a comprehensive database and blood biobank of population entering old age in rural and urban areas of Korea.

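### One unqualified P<0.05 rule also covers the phase I marker search, where a false discovery rate rule is needed

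*Protocol article*

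**What the plan says.** The Statistical analysis section of the protocol article opens broadly: "We will conduct various analyses within the cohort". It then lists descriptive summaries, linear and logistic regression, mixture models, survival methods and prediction modelling. On comparisons it says that "group differences (between KM-based phenotypes or between rural and urban areas) will be analyzed using Student"'s t test and analysis of variance. It ends with the threshold: "P values less than 0.05 will be considered to indicate statistical significance". The article sets no different rule for any class of analysis, names no primary hypothesis and does not label any result as exploratory.

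The aim is stated elsewhere. The Results section says of the baseline phase that "we will focus on identifying markers for KM-based phenotypes and examining how these phenotypes relate to aging and associated diseases". The Discussion says of phase I that "our initial focus is on identifying diagnostic markers that enable the application of KM by conducting multi-omics analyses".

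The material to be searched is in Table 1, row 11 (Clinical laboratory). It has a biochemistry list ("The biochemistry will be used to check the levels of Albumin, AST, TP, Total bilirubin" and others), a hormone list ("The hormones to be checked are 25-OH Vitamin D, Osteocalcin, Cortisol, Free T4, TSH" and others), a haematology list, urine tests, a bead-based multiplex protein assay, and this: "GC/LC-MS based untargeted metabolomics analysis will be conducted to profile the comprehensive metabolic data from blood of participants". The notes to Table 1 name four KM phenotype factors: kidney deficiency, five organ deficiency, blood stasis and core seven-emotions status.

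**The concern.** A threshold of 0.05 limits the error of one test. Applied feature by feature to a screen, it admits about one null association in twenty, however many features are tested. An untargeted platform is by design a search over many features with no prior hypothesis for each, so the stated rule suits that part of the study worst, and that part is the lead aim of phase I.

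At stake is the credibility of the phase I markers. The Discussion gives them a working role in applying KM, and later work on age-related symptoms and diseases is to follow from this step. A list with an unknown and possibly large share of false entries is a weak basis for either.

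**Working it through.** **What can be reproduced.** The plan gives no error rate or power figure for the marker search. Its only numbers are the 0.05 threshold and the sample size of 1,000. The latter comes from a population share, not from a power calculation: 1% of 82,498 is 825; allowing for 20% dropout gives 825 × 1.2 = 990 or 825 / 0.8 ≈ 1,031, so 1,000 is a rounded figure. It says nothing about how many tests 0.05 can bear.

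**Inputs from the article**
- Named blood analytes, counted from Table 1, row 11: biochemistry 22, hormones 15, haematology 14; 22 + 15 + 14 = 51.
- KM phenotype factors: 4 (notes to Table 1).
- α = 0.05 (Statistical analysis); two-sided is assumed, as sidedness is not stated.

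**Inputs assumed, because the article does not give them**
- Omics features, metabolomics and proteins together: 100 to 3,000.
- Share of tested associations that are real (π): 2% to 20%.
- Power per real association: 80%, with 50% and 100% as checks.

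**Step 1. Expected false positives, named analytes only.** Tests: 51 × 4 = 204. If none is real, 0.05 × 204 = 10.2. If 10% are real, 0.05 × 0.90 × 204 = 9.2. Correlation between analytes does not change these expectations. Within one phenotype the expectation is 0.05 × 51 = 2.6, and the chance of at least one false positive is 1 − 0.95^51 = 93%. That last figure does assume independent tests.

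**Step 2. Adding omics features.** Tests = (51 + features) × 4; expected false positives if none is real = 0.05 × tests.

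| Assumed omics features | Tests | Expected false positives |
|---|---|---|
| 100 | 604 | 30 |
| 300 | 1,404 | 70 |
| 1,000 | 4,204 | 210 |
| 3,000 | 12,204 | 610 |

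**Step 3. False share of declared markers.** Share = α(1 − π) / [α(1 − π) + power × π]. At 80% power:
- π = 2%: 0.049 / (0.049 + 0.016) = 75%
- π = 5%: 0.0475 / (0.0475 + 0.040) = 54%
- π = 10%: 0.045 / (0.045 + 0.080) = 36%
- π = 20%: 0.040 / (0.040 + 0.160) = 20%

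The share passes one half when π is below α / (α + power): 0.05 / 0.85 = 5.9% at 80% power, 0.05 / 0.55 = 9.1% at 50% and 0.05 / 1.05 = 4.8% at 100%. A larger sample does not cure this: at 100% power and π = 5% the share is 0.0475 / 0.0975 = 49%.

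**Step 4. Effect of the remedy.** Flat 0.05 was simulated against Benjamini-Hochberg at 5% (1,000 runs per setting; independent tests; 500 v 500; 204, 1,404 and 4,204 tests; π of 2%, 5% and 10%).

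| | Flat 0.05 | Benjamini-Hochberg 5% |
|---|---|---|
| False share | 31% to 73% | about 4% to 6% |
| Power, 0.3 SD difference | above 99% | 93% to 97% |
| Power, 0.2 SD difference | about 88% | 34% to 58% |

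The procedure was applied once across all tests in each run. Applying it within platforms, or with unequal phenotype groups, would shift the power figures.

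**The case against.** The strongest reply is that this is a condensed article about an observational cohort. The Statistical analysis section does not name the omics analysis, protocol version 1.3 is not shown, and an analysis plan may hold feature-level error control. Closing such a section with an alpha level is routine. This stands in part: a reader might infer that the study has no multiplicity control anywhere, and the article cannot establish that. What it does establish is a decision rule stated without limit, in a section that covers the cohort's analyses generally, beside a lead aim for which the rule is unsuitable. If another document holds a correction, this sentence still has to be reconciled with it. The suggestion that the P values meant are already adjusted has no support in the text.

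Two stronger readings are tempting and do not hold.

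- A reader might infer that most declared markers will be false. That needs fewer than about 5.9% of associations to be real at 80% power. The documents give no such share, no power and no feature count; if 20% are real, the false share is 20%.
- A reader might infer that false markers feed straight into the randomised trials. The Discussion tailors phase II to KM phenotypes, which are assessed by questionnaire. It does not say that a marker list selects participants, and the phase II details are left to separate publications.

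It is also fair to say that a discovery study can accept some false leads. That argues for a false discovery rate over strict family-wise control. It does not argue for presenting unadjusted results as significant.

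**Conclusion.** The point holds for the rule as stated. Followed literally, it yields about 10 expected false positives from the 204 tests on named analytes if none is real. This figure rests only on counts in the article, the 0.05 threshold and one test per analyte and phenotype factor. Omics features add to it by an amount that cannot be fixed without the feature count. The false share could be substantial, but its size, including the 36% and 54% examples, depends on the assumed prevalence of real associations and on power. The consequence supported by the text is a less reliable phase I marker list, not a flawed phase II selection rule. This is a should-fix matter: the study can run as designed, but the sentence ought to be amended before the marker analyses are done.

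**What to change.** Keep 0.05 for the other analyses and add after the existing sentence:

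> Laboratory and omics marker screens will be declared at a Benjamini-Hochberg false discovery rate of 5% within each platform, across all features and phenotypes; other p values without a prespecified primary hypothesis are exploratory and reported with effect sizes and 95% CIs.

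A family-wise adjustment for a small confirmatory set should be added only if the sponsor names that set. If the full protocol or analysis plan already controls the marker screens, it is enough to state that rule here.

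The change affects wording and analysis only; no visit, sample or measurement changes. The cost is a shorter marker list and less power for small effects: in the simulation above, power for a 0.2 SD difference falls from about 88% to between 34% and 58%, while a 0.3 SD difference keeps 93% to 97%. If effects near 0.2 SD matter, the sponsor could state a looser false discovery rate or a discovery and validation split in advance.

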### Patient and public involvement

Patients and/or the public were not involved in this research’s design, conduct, reporting, or dissemination plans as it describes a protocol.

### Ethics and dissemination

This study received approval from the Institutional Review Board (IRB) of Wonkwang University Korean Medicine Hospital, Iksan, Republic of Korea (approval number: WKUIOMH-IRB-2023-05) on August 16, 2023 and Jangheung Integrative Medical Hospital (approval number: WKUJIM-202307-001) on August 21, 2023. Written informed consent will be obtained from all participants prior to their enrollment in the study. This study is registered with the Clinical Research Information Service (https://cris.nih.go.kr/cris/en/) (KCT0008863), and the current protocol version is 1.3. The results from this cohort study will be disseminated through the publication of peer-reviewed manuscripts, presentations at scientific meetings, and/or conferences.

## Results

In the baseline phase of this study, we will focus on identifying markers for KM-based phenotypes and examining how these phenotypes relate to aging and associated diseases. In the next phase, we will implement interventions tailored to KM-based phenotypes to verify the effects of KM on healthy aging. Ultimately, we intend to develop a KM-based integrated health management model, with further substudies aiming to explore factors related to healthy aging.

## Discussion

South Korea is currently navigating the challenges of transitioning into a super-aged society, emphasizing the critical importance of proactive health management for healthy aging before individuals reach the age of 65 years [1–5]. This paper outlines a multifaceted research protocol aimed at revealing the complexities associated with aging in both urban and rural settings, considering the distinctive characteristics that are prevalent in various regions of Korea. Data collection for this study began in August 2023 and is being carried out in two phases. Phase I comprises a cross-sectional cohort study (baseline) detailed in this paper. Participants who are included in the cohort will be given the option of allowing their data to be used for analyses and identifying them for future research interventions or for comparison purposes for intervention trials. Details of the phase II interventions will be published in full manuscripts separately.

In particular, a key aspect of our study involves analyzing KM-based phenotypes to examine aging patterns and certain diseases associated with each phenotype and evaluating the KM-based integrated health management model. To achieve this goal, in phase I, our initial focus is on identifying diagnostic markers that enable the application of KM by conducting multi-omics analyses, including hormone, immune, metabolite markers. We will subsequently explore age-related symptoms or vulnerable diseases associated with KM phenotypes through cohort studies. In phase II, we plan to conduct multiple randomized controlled trials that apply interventions such as community programs specifically tailored to well-defined KM-based phenotypes identified in phase I to verify the effects of KM on healthy aging. Based on these results, we intend to develop an integrated health management model for healthy aging, and establish a comprehensive database and blood biobank of population entering old age in rural and urban areas of Korea.

In addition, this study will include various physical function assessments, such as range of motion assessments for the knee and lumbar joints, McGill’s core endurance test, bone density tests and bioelectric impedance analysis. These assessments are expected to provide information on muscle atrophy, osteoporosis, and core muscle weakness, which are currently discussed in relation to health issues and functional decline associated with aging [39,40]. Additionally, mental health assessments and EEG analysis will be used to evaluate cognitive and emotional functions, offering insights into psychological changes associated with aging. The study will also explore the connection between physical and psychological decline and various blood markers, including multi-omics data, to provide a comprehensive understanding of age-related health deterioration.

We have established the target number of participants for this cohort at 1,000. Although this number has limitations in representing the entire population of old age, it is equivalent to 1% of the target population, based on the demographic distribution of medium-sized cities and rural areas of South Korea, taking into account the duration and scope of this project. Despite the relatively modest sample size, the study’s strength lies in its potential to reveal connections between KM-based phenotypes and aging patterns. It also aims to provide an integrated health management model that incorporates thorough diagnosis and an integrative medical treatment strategy.

## Abbreviations

CRCs: Clinical Research Coordinators
IRB: Institutional Review Board
KM: Korean medicine
KoMAC: The Korean Medicine for Aging Cohort
WHO: World Health Organization.
